### 6.3 Complier average causal effects analysis

This will be performed by two stage least squares regression analysis on **PPACS**. The definitions for compliers and non-compliers/treatment not received is given in 4.3. As is standard practice for CACE analysis, it is assumed that there is no effect of being randomized to a particular group, other than the effect that results from receiving the intervention in practice (with at least 4 visits).

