### 1560 1561 4.3 Complier average causal effects (CACE) population

1562 A secondary analysis will be undertaken, using a CACE analysis to determine the effect of receiving the  
1563 intervention, rather than merely being randomised to receive it. For the purposes of this analysis, we define  
1564 “receiving the intervention” to mean that the family has attended at least four of the six planned intervention  
1565 visits, and “not receiving the intervention” as receiving zero to three sessions. These first four sessions relate to  
1566 delivery of the core intervention, with the extra two sessions being booster sessions. Delays to the planned  
1567 schedule will not be considered a protocol violation, so long as at least four of the six planned intervention visits  
1568 were completed before the outcome is assessed. Initially all families in the control group will be analysed as not  
1569 receiving the intervention (unless, off protocol, they receive at least four sessions of the ViPP intervention).

1570 A sensitivity analysis will be undertaken on this CACE analysis, where families who receive some other video  
1571 feedback intervention during the study (off protocol) will be analysed as if they received the intervention (unless  
1572 we know that they received an incomplete course, and that this incomplete course consisted of no more than  
1573 three sessions).

1574 A further CACE analysis will be performed, to determine the effect of receiving the intervention to a high level  
1575 of fidelity, rather than merely being randomised to receive it (and rather than receiving it with poor fidelity). To  
1576 count as receiving the intervention, families would have to receive at least four sessions with a mean level of  
1577 fidelity above the 25th centile (and then above the 50th centile) of the distribution of fidelity scores within this  
1578 randomized trial.

1579

1580 **Change from official signed draft:** previously there was a per protocol population definition described here,  
1581 rather than a complier average causal effects population.

1582 **Change from version 1 to version 2:** a new CACE analysis is added which refers to fidelity as well as to  
1583 number of sessions received.

1584

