**This section replaces the per protocol analysis in the official signed draft.**

### 6.4 Secondary Efficacy Analysis

The impact of the intervention on the secondary measures assessing child behaviour and parental outcomes, will be assessed using the same approach as for the primary endpoint, with the same treatment of missing values for CBCL and SDQ, and a different treatment of missing values that does not involve multiple imputation for all other outcomes, as detailed above. Secondary outcomes which are measured on both parents/ care-givers: namely child behaviour (SDQ and CBCL), (parental couple functioning (assessed using RDAS), parental mood (assessed using PHQ9), parenting practice (assessed using the Parenting Scale), and parental anxiety (assessed using GAD7)) will be analysed separately by gender. In the case where both the primary and secondary care-givers are included in this study and both are of the same gender, the mean score of the two will be calculated and used in the analysis in order to avoid violating assumptions of independence. Parental sensitivity may be added here and analysed in the same way (subject to separate funding being received for its measurement).

**Changes from official signed draft:** AUDIT assessment of alcohol consumption is no-longer being analysed as a secondary outcome.

**Change from SAP version 1.0:** The outcomes included in the secondary outcomes have been clarified. This paragraph now corresponds to the analysis methods written into the footnotes of the tables (i.e. the tables of this current SAP and also in the previous SAP version 1.0). The analysis methods for SDQ and CBCL was not mentioned in the text of the previous SAP, so the tables was the only source for information that clarified their method of analysis in SAP version 1.0.

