| Child behaviour (CBCL) (secondary care-giver reported)                    |            |           |               |           |                           |         |
| Baseline                                                                  |            |           |               |           |                           |         |
| 5 month follow-up                                                         |            |           |               |           |                           |         |
| 24 month follow-up                                                        |            |           |               |           |                           |         |
| Strengths and Difficulties of Child (SDQ) (secondary care-giver reported) |            |           |               |           |                           |         |
| Baseline                                                                  |            |           |               |           |                           |         |
| 5 month follow-up                                                         |            |           |               |           |                           |         |
| 24 month follow-up                                                        |            |           |               |           |                           |         |

1892 n=number of children with outcome reported by specified care-giver

1893 Treatment effect is the difference in mean between treatment groups from regression analysis of the outcome measure on the baseline score  
1894 of that same measurement, on treatment centre, on randomised group, on length of follow-up, on age of child and on number of parents/  
1895 care-givers participating (all treated as fixed effects).

1896 **Change from official signed draft:** Results on secondary care-givers have been added to the above table. Surplus columns on sample size  
1897 (which were never intentionally included) have been removed.  
1898

1899  
1900

8.8    **Table: Causal Average Complier Effects analysis on Primary and Secondary Outcomes of Child Behaviour**

| Randomised Group:                                                         | ViPP Group |           | Control Group |           | Treatment Effect
Effect
(95% CI) | p-
value |
|---------------------------------------------------------------------------|------------|-----------|---------------|-----------|----------------------------------------|-------------|

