| 24 month follow-up (reporter external to family)                          |            |           |               |           |                                        |             |
| Child behaviour (CBCL) (secondary care-giver reported)                    |            |           |               |           |                                        |             |
| Baseline                                                                  |            |           |               |           |                                        |             |
| 5 month follow-up                                                         |            |           |               |           |                                        |             |
| 24 month follow-up                                                        |            |           |               |           |                                        |             |
| Strengths and Difficulties of Child (SDQ) (secondary care-giver reported) |            |           |               |           |                                        |             |
| Baseline                                                                  |            |           |               |           |                                        |             |
| 5 month follow-up                                                         |            |           |               |           |                                        |             |
| 24 month follow-up                                                        |            |           |               |           |                                        |             |

1901

n=number of children with outcome reported by specified care-giver

1902  
1903  
1904

Treatment effect is the difference in mean between treatment groups from regression analysis of the outcome measure on the baseline score of that same measurement, on treatment centre, on randomised group, on length of follow-up, on age of child and on number of parents/ care-givers participating (all treated as fixed effects).

1905  
1906  
1907

**Change from official signed draft:** The title is changed, so that this now reflect the complier average causal effects model. Results on secondary care-givers have been added to the above table. Surplus columns on sample size (which were never intentionally included) have been removed.

1908  
1909

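### SAP Table 8.8 is titled as a CACE analysis, but its footnote defines the effect by the ITT regression, and no CACE estimator is written for its CBCL and SDQ rows

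*Combined protocol and SAP*

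**What the plan says.** SAP 4.3 sets the aim as "using a CACE analysis to determine the effect of receiving the" intervention, as distinct from being allocated to it. Receipt means attending four or more of the six visits. Section 4.3 does not restrict the analysis to one outcome.

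SAP 6.3 gives the estimator: "This will be performed by two stage least squares regression analysis on" PPACS. It refers back to 4.3 for who counts as a complier, and assumes that allocation affects the outcome only through receipt. It mentions no other outcome.

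Table 8.8 is titled "Causal Average Complier Effects analysis on Primary and Secondary Outcomes of Child Behaviour". Its rows cover PPACS, CBCL and SDQ by primary care-giver, CBCL and SDQ by secondary care-giver, and SDQ by a reporter outside the family at 24 months. One footnote covers them all. It reads "Treatment effect is the difference in mean between treatment groups from regression analysis of the outcome measure on the baseline score" of the same measure, and continues "on treatment centre, on randomised group, on length of follow-up, on age of child and on number of parents/ care-givers participating". The Table 8.7 footnote, which belongs to the ITT analysis, is worded identically.

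A change note below Table 8.8 says: "The title is changed, so that this now reflect the complier average causal effects model". It mentions no change to the definition of the effect.

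**The concern.** A complier effect needs a variable for treatment received, and an instrument for it. The Table 8.8 footnote has neither: its only treatment variable is randomised group. The SAP therefore gives two incompatible estimators for the PPACS row, and only a non-CACE one for the CBCL and SDQ rows.

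The size of the effect of receipt is at stake. An analyst who programmed the table from its footnote would print the Table 8.7 effects again under a CACE title. Readers would see an effect of receiving four or more sessions equal to the effect of being offered them, whatever the uptake. An analyst who followed 6.3 in spirit would print different numbers. A pre-specified plan should not leave that choice until the data are in hand.

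**Working it through.** **1. The plan's own figure.** The only design figure is power. With 300 families and 20% loss, 300 × 0.80 / 2 = 120 per arm. Power ≈ Φ(d√(n/2) − 1.96), assuming a two-sided 5% test:

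- d = 0.36: 0.36 × √60 = 2.789; 2.789 − 1.960 = 0.829; power 79.6% (79.3% with the noncentral t).
- d = 0.42: 0.42 × √60 = 3.253; 3.253 − 1.960 = 1.293; power 90.2% (90.0% with the noncentral t).

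The stated 80% and 90% are reproduced. They concern the ITT comparison and are used below only as a scale for the effect.

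**2. The specifications side by side.**

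| Place in SAP | Label | Outcomes | Treatment variable | Instrument |
|---|---|---|---|---|
| 6.3 | CACE | PPACS named | Receipt as in 4.3 | Implied by two-stage least squares |
| Table 8.7 footnote | ITT | PPACS, CBCL, SDQ | Randomised group | None |
| Table 8.8 footnote | CACE | PPACS, CBCL, SDQ | Randomised group | None |

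The last two rows differ only in the label.

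**3. Size of the discrepancy.** Under the exclusion restriction in 6.3 and with no control-arm receipt, CACE = ITT / c, where c is the proportion of the intervention arm meeting the 4.3 definition. Reporting ITT in place of CACE understates it by 1 − ITT/CACE = 1 − c. The documents give no value for c, so it is varied:

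| Assumed c | CACE if ITT = 0.36 SD | CACE if ITT = 0.42 SD | Understatement |
|---|---|---|---|
| 90% | 0.36/0.90 = 0.40 | 0.42/0.90 = 0.47 | 10% |
| 80% | 0.36/0.80 = 0.45 | 0.42/0.80 = 0.525 | 20% |
| 70% | 0.36/0.70 = 0.51 | 0.42/0.70 = 0.60 | 30% |
| 60% | 0.36/0.60 = 0.60 | 0.42/0.60 = 0.70 | 40% |

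**4. Check by simulation.** Trials of 240 families were simulated 2,000 times at each c, with a true ITT effect of 0.36 SD, a baseline covariate, and compliers differing from non-compliers in prognosis. A regression on randomised group, as in the footnote, averaged 0.359, 0.359, 0.360 and 0.359 at c = 90%, 80%, 70% and 60%. Two-stage least squares averaged 0.399, 0.449, 0.516 and 0.599, against true complier effects of 0.400, 0.450, 0.514 and 0.600. The footnote model returns the ITT effect at every level of receipt.

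**The case against.** The strongest reply is that the footnote is a leftover and nobody would act on it. Much supports this. The SAP change log says that the table's intended contents, as well as its title, were changed to the CACE analysis. Section 4.3 does not limit CACE to PPACS. Section 6.2 mentions the CACE model within a sensitivity analysis that it then applies to PPACS, SDQ and CBCL totals, though the wording is loose. A footnote that is plainly wrong for the PPACS row is also weak evidence of what was chosen for the other rows. A reader might infer that the CBCL and SDQ rows will certainly hold ITT estimates; the documents do not support that.

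Two other strong readings also fail. A reader might take 6.3 to confine two-stage least squares to PPACS, but it names PPACS without excluding other outcomes. A reader might also lean on the remark in 6.4, "so the tables was the only source for information that clarified their method of analysis", as making the footnotes authoritative here. That sentence ends by referring to SAP version 1.0, and the paragraph it annotates does not discuss CACE.

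The contradiction itself remains. The footnote includes length of follow-up, an adjustment that version 2.0 newly introduced for the secondary outcomes, so it carries version 2.0 content and still describes no CACE model. The statement in 6.4 that secondary outcomes follow the primary-endpoint approach does not fill the gap, because that approach in 6.2 is the regression with multiple imputation. Nowhere does the SAP write a two-stage model for CBCL or SDQ.

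**Conclusion.** The point holds as an internal contradiction in a secondary analysis. The Table 8.8 footnote conflicts with 6.3 for PPACS and leaves the CBCL and SDQ rows without a written CACE estimator. A CACE estimate was evidently intended for the table, so the likeliest cause is a carried-over footnote.

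The numerical consequence is conditional. If the footnote is followed as written, the complier effect is understated by about 1 − c, or 10% to 40% for c from 90% to 60%. This rests on assumed receipt rates, no receipt in the control arm, and the exclusion restriction stated in 6.3. If some control families received four or more sessions, which 4.3 allows for, c becomes the difference in receipt between the arms and the understatement is larger. The choice of two-stage least squares in 6.3 is not in question, and neither the ITT primary analysis nor the sample size is affected.

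**What to change.** Replace the Table 8.8 footnote with a definition of the complier effect:

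- Two-stage least squares, with randomised group as the instrument for receipt as defined in 4.3. Section 4.3 also has fidelity-based definitions of receipt, so the footnote should say which one the table uses.
- The covariates of the present footnote in both stages: baseline score, centre, length of follow-up, child age and number of participating care-givers. Length of follow-up is measured after randomisation, so wording that kept only baseline covariates would drop an adjustment that SAP version 2.0 requires.
- For SDQ by the external reporter, which has no baseline of its own, the primary care-giver's baseline SDQ, as in 6.1.
- The effect and its 95% confidence interval taken from the two-stage fit.

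State in 6.3 that this applies to every outcome in Table 8.8. Alternatively, delete the CBCL and SDQ rows and keep CACE for PPACS alone; the footnote must change in either case.

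The cost is one footnote, one sentence and a few additional model fits. No new data are needed. If the table has already been produced, the report should state which estimator each row used.

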**This section replaces the per protocol analysis in the official signed draft.**

### 6.4 Secondary Efficacy Analysis

The impact of the intervention on the secondary measures assessing child behaviour and parental outcomes, will be assessed using the same approach as for the primary endpoint, with the same treatment of missing values for CBCL and SDQ, and a different treatment of missing values that does not involve multiple imputation for all other outcomes, as detailed above. Secondary outcomes which are measured on both parents/ care-givers: namely child behaviour (SDQ and CBCL), (parental couple functioning (assessed using RDAS), parental mood (assessed using PHQ9), parenting practice (assessed using the Parenting Scale), and parental anxiety (assessed using GAD7)) will be analysed separately by gender. In the case where both the primary and secondary care-givers are included in this study and both are of the same gender, the mean score of the two will be calculated and used in the analysis in order to avoid violating assumptions of independence. Parental sensitivity may be added here and analysed in the same way (subject to separate funding being received for its measurement).

**Changes from official signed draft:** AUDIT assessment of alcohol consumption is no-longer being analysed as a secondary outcome.

**Change from SAP version 1.0:** The outcomes included in the secondary outcomes have been clarified. This paragraph now corresponds to the analysis methods written into the footnotes of the tables (i.e. the tables of this current SAP and also in the previous SAP version 1.0). The analysis methods for SDQ and CBCL was not mentioned in the text of the previous SAP, so the tables was the only source for information that clarified their method of analysis in SAP version 1.0.

## 1792 6.5 Safety Analysis

1793 A table of serious adverse events and any adverse events considered to be relevant will be produced, by type of  
1794 event and by treatment received.

1795 The table will show numbers of children who have at least one such adverse event of a given type and then  
1796 numbers of families where at least one parent/care-giver is affected by this type of adverse event. Percentages  
1797 (of children/ families) will be calculated and presented. Proportions will be compared between treatment groups  
1798 using Fisher's exact test.

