## **6. STUDY Design**

The study is a two-arm, parallel group, researcher-blind, randomised controlled trial (RCT), to test the clinical and cost effectiveness of a video-feedback intervention (ViPP-SD) for parents of young children (12-36 months) at risk of behavioural difficulties. The trial will involve 300 families, who will be randomly allocated into one of two groups:

- (1) The intervention group, who will receive the video-feedback intervention (described below) (n=150) plus treatment as usual
- (2) Treatment as usual (control group) (n=150)

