## 1260 **eDocument 2. Pre-specified statistical analysis plan**

### 1261 **Additional details for statistical policies**

1262 Continuous/numeric variables that follow an approximately normal distribution are summarised using the mean  
1263 and standard deviations. Skewed variables are summarised using the median and inter-quartile range.  
1264 Categorical variables are presented as frequencies and percentages. Scores from psychometric scales are treated  
1265 as numeric. Histograms and box-plots are used to assess distributional assumptions and to check for possible  
1266 outliers. The significance level for statistical tests is set at 5%. The primary analysis was conducted on an  
1267 intention to treat basis. The safety population comprises children and their parents/ caregivers who had received  
1268 at least one intervention session as part of the VIPP-SD programme plus those allocated to the usual care group  
1269 who did not receive any VIPP intervention. All analyses (unless indicated otherwise) were undertaken using  
1270 Stata version 13 and 15 following a pre-specified statistical analysis plan.

1271

1272

1273

1274

1275

**Statistical Analysis Plan (SAP) version 2.0  
for Healthy Start, Happy Start**  
Based on protocol version 6.0

Principal Investigator: [name]

Study Investigators (alphabetically):  
[name]  
[name]  
[name]  
[name]  
[name]  
[name]  
[name]

Study Management Team: [name] and [name]

SAP Working Group: [name] and [name] ([name] and [name] for the economics section)

| Version | Date       | Lead Author |
|---------|------------|-------------|
| 2.0     | 7 May 2019 | [name] |

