### 3.10 Randomisation

Randomisation lists were prepared by a statistician independent of the trial ([name]) using computer generated 1:1 allocation (ViPP intervention vs treatment as usual) and variable block sizes. Randomisation will be stratified by treatment centre and by number of parents/ care-givers participating (one or two). The randomisation lists (one for each strata) will be uploaded on to InForm (the study electronic data capture system) and eligible subjects allocated online to the next available treatment code in the appropriate randomisation list.

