## 1652 **6 Statistical Methodology**

### 1653 **6.1 General Methodology**

1654 **Descriptive data:** Continuous/ numeric variables that follow an approximately Normal distribution will be  
1655 summarised using the mean and standard deviations. Skewed variables will be summarised using the median  
1656 and inter-quartile range. Categorical variables (binary and ordinal and multinomial) will be presented as  
1657 frequencies and percentages. Scores from psychometric scales will be treated as numeric.

1658

1659 **Statistical models to be used for obtaining estimates of the treatment effect on child behaviour outcomes:**  
1660 These statistical models will have either PPACS score or CBCL score or SDQ at follow-up (based on  
1661 assessment by the primary or secondary -care giver) as the outcome, and will be adjusted by baseline  
1662 measurements of the same score, time from randomisation to follow-up assessment, recruitment centre, age of  
1663 child at recruitment and parental involvement (one or two parents/ care-givers) as fixed effects. SDQ measured  
1664 by a teacher/ some-one external to the family, will be adjusted for primary care-giver SDQ at baseline.

1665  Adjusting for centre as a random effect, although planned in the protocol, will not be statistically robust owing  
1666 to there being only a very small number of centres. As an alternative, centre has been included as a fixed effect  
1667 in the proposed model.

1668

1669 **Checking of assumptions underlying hypothesis tests and models:** Histograms and box-plots will be used to  
1670 assess the distributional assumptions required for the models that will be fitted and to check for possible  
1671 outliers. Log transformations will be applied, where appropriate, in order to render outcomes variable  
1672 distributions closer to the Normal. If neither the variable itself nor its log result in residuals from the regression  
1673 analysis that are close enough to the Normal distribution to allow regression results to be reported confidently,  
1674 then boot-strap techniques will be undertaken to calculate confidence intervals, after relaxing the assumptions of  
1675 normality. The relationship between the outcomes and other variables will be explored graphically, using scatter  
1676 plots and box-plots.

1677 **Statistical significance level:** Results will be interpreted according to a 5% significance level.

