| Elements of intervention completed (%):                                             |                  |            |            |            |           |  |  |  |  |  |
| Speak for child                                                                     |                  |            |            |            |           |  |  |  |  |  |
| Attachment messages                                                                 |                  |            |            |            |           |  |  |  |  |  |
| Set Message                                                                         |                  |            |            |            |           |  |  |  |  |  |
| Set Explanation                                                                     |                  |            |            |            |           |  |  |  |  |  |
| Exploration of messages                                                             |                  |            |            |            |           |  |  |  |  |  |
| Duration of video recording: Mean (SD)                                              |                  |            |            |            |           |  |  |  |  |  |
| Duration of visit, therapist reported: Mean (SD)                                    |                  |            |            |            |           |  |  |  |  |  |

1957

1958

1959

1960

1961

1962 8.17 Table: Adverse Events

|                                                                                                     | Received ViPP (at
least one appointment) | Allocated to control
group (and did not
receive any
appointments for ViPP) |                                                                             |
|-----------------------------------------------------------------------------------------------------|---------------------------------------------|-------------------------------------------------------------------------------------|-----------------------------------------------------------------------------|
|                                                                                                     | (n=number of
families)                   | (n=number of families)                                                              | p-value by
Fisher's exact
test for
difference
between
groups |

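### Adverse events are compared between groups only by a Fisher p-value for each event category, with no effect estimate, confidence interval or any-SAE row

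*Combined protocol and SAP*

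**What the plan says.** SAP 6.5 (Safety Analysis) plans a table of serious and other relevant adverse events by type and by treatment received. It counts children with at least one event of a type, and families in which at least one care-giver had one. Percentages follow, and then the comparison: "Proportions will be compared between treatment groups" "using Fisher's exact test".

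The shell of Table 8.17 matches this. It has n (%) in each group and a last column headed "p-value by Fisher's exact test for difference between groups". The serious-event rows, for the child and for care-givers, are by category. There is no column for a difference, ratio or interval, and no row for any SAE.

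The significance level is general. SAP 6.1 states "Results will be interpreted according to a 5% significance level", and the statistical policies that precede the SAP also set 5% for statistical tests. Neither treats safety separately, and neither says whether tests are one- or two-sided.

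The outcome tables (8.7 to 8.12) are built differently: each has a column for the treatment effect with a 95% CI.

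**The concern.** For benefit, the SAP estimates an effect and shows its uncertainty. For harm, the only planned between-group inference is a p-value, category by category. Splitting serious events by category thins the counts, and a thin row is likely to be non-significant whether or not the intervention does harm. The p-value does not show how large an excess of events remains compatible with the data. That excess matters for a programme which the protocol's rationale (section 2) proposes for wide delivery in the NHS if it proves effective.

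**Working it through.** **Inputs**
- Families per group: 150 (protocol section 6, "Treatment as usual (control group) (n=150"), randomised 1:1 (SAP 3.10).
- Test and level: Fisher's exact test (SAP 6.5) at 5% (SAP 6.1). Two-sided is assumed because the documents do not say.
- Background event rate: not given. Assumed range 1% to 10%.
- Safety groups: by treatment received (SAP 4.2). Families allocated to ViPP who attend no session are not in the ViPP group, so 150 is in effect an upper limit for it.

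**The plan's own power figure.** The only one is for efficacy (SAP 3.6): 80% and 90% power at effect sizes 0.36 and 0.42 with 120 per group. The noncentrality is d × √(120/2), which is 0.36 × 7.746 = 2.789 and 0.42 × 7.746 = 3.253. The normal approximation gives Φ(2.789 − 1.960) = 79.6% and Φ(3.253 − 1.960) = 90.2%. The t distribution gives 79.3% and 90.0%. The figure reproduces. No power or precision is stated for safety.

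**Chance that the planned test misses an increase.** For true risks p₁ (ViPP) and p₀ (control), power is the sum, over all pairs of counts (x, y) with Fisher p ≤ 0.05, of Bin(x; 150, p₁) × Bin(y; 150, p₀). The chance of a miss is one minus power.

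| Control risk (assumed) | ViPP risk | Power | Missed |
|---|---|---|---|
| 1% | 2% | 0.022 | 98% |
| 2% | 4% | 0.088 | 91% |
| 3% | 6% | 0.152 | 85% |
| 5% | 10% | 0.298 | 70% |
| 10% | 20% | 0.629 | 37% |
| 1% | 3% | 0.098 | 90% |
| 2% | 6% | 0.305 | 70% |
| 3% | 9% | 0.505 | 50% |
| 5% | 15% | 0.797 | 20% |

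**Sensitivity at 5% against 10%.** With 140 or 135 ViPP families against 150 controls, 67% or 66% are missed. (The slight fall comes from the discreteness of the test.) With 120 per group, 78% are missed; with a one-sided test at 150 per group, 59%. Power of 80% would need about 474 per group (435 without continuity correction).

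**What an interval would show.** Take 6/150 against 3/150. Fisher p = 0.50. The difference is 0.040 − 0.020 = 0.020. The Wilson limits are 0.0185 to 0.0845 and 0.0068 to 0.0571. Newcombe's method gives:
- lower limit: 0.020 − √[(0.040 − 0.0185)² + (0.0571 − 0.020)²] = −0.023
- upper limit: 0.020 + √[(0.0845 − 0.040)² + (0.020 − 0.0068)²] = +0.066

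With 15/150 against 8/150, p = 0.19 and the difference is +4.7 points (95% CI −1.5 to +11.1). With no control events, 5 against 0 gives p = 0.060 and 6 against 0 gives p = 0.030.

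**The case against.** Several objections have force.

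- **Low expected risk is not a low event rate.** A reader might infer from SAP 5.3 that events will be few and nearly every row non-significant. The text does not support that. The low risk it describes is harm from the intervention. The same section collects all serious events in the child and participating care-givers throughout follow-up, whatever their cause, and follow-up is two years. The background rate is unknown and could be appreciable.
- **The 70% figure depends on an assumption.** The 5% control risk behind it appears nowhere in the documents. Only the range can be stated, and it is wide.
- **Nothing is withheld.** Counts, percentages and denominators are shown by group, so a reader can derive a difference and an interval. It is too strong to say that the size of a compatible harm cannot be seen; it is simply not planned for reporting.
- **Harm is assessed in other ways.** The Chief Investigator reviews each SAE, related and unexpected events go to the ethics committee, and the DMEC reviews SAE reports. Worsening child behaviour, parental mood or anxiety would appear in outcome tables that do carry intervals. None of these, however, estimates the between-group difference in SAEs.
- **No passage equates non-significance with safety.** A reader might infer that the trial will declare no harm from a non-significant test. The SAP has only its general 5% statement. The misreading is left open, not planned.
- **An interval does not add information.** The trial was sized for PPACS, and imprecision on rare events is inherent. This is true, but an interval shows the imprecision and a lone p-value does not. It is no reason to delete the p-value.
- **The table is a blank shell.** Rows by category do not forbid a total. Even so, neither SAP 6.5 nor Table 8.17 asks for one.

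**Conclusion.** The point holds as a weakness in how harm will be reported. The comparison planned in SAP 6.5 and Table 8.17 is a Fisher p-value for each category beside n (%), without an effect estimate, interval or overall SAE row. For assumed background risks of 1% to 10% and 150 families per group, that test misses a doubling between 98% and 37% of the time. These figures rest on the assumed rates, a two-sided test and the full randomised number in each group. Modest departures in group size, or a one-sided test, leave the conclusion unchanged.

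The primary efficacy result, data collection and case-by-case SAE review are unaffected. Fisher's test is a valid choice for sparse counts; the gap is that nothing planned beside it shows what difference the data can exclude.

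**What to change.** In SAP 6.5 and Table 8.17:

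1. Add one row for any SAE in the child and one for any SAE in a participating care-giver, counted once per family, with the safety-population denominators.
2. For each, give the risk difference (ViPP minus control) with a 95% CI by the Newcombe or an exact method. Name the method in the SAP.
3. Keep the Fisher p-value beside it if wanted. Sparse individual categories can be given as counts and percentages.
4. State that safety is interpreted from the interval, and that a non-significant test is not evidence of no harm.

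The last statement also settles cases where test and interval disagree. For 5/150 against 0/150, Fisher p = 0.060, while the Newcombe interval is +0.2 to +7.6 points.

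The cost is a change of wording and slightly more analysis on data already collected. The downside is a less reassuring safety statement.
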